### Sample size and sampling technique

The targeted sample size for this study was determined by previous studies evaluating the agreement between food frequency questionnaires (FFQs) and 24-hour dietary recalls. These studies have found correlation coefficients (r) ranging from 0.3 to o.7, indicating moderate to strong agreement between the two dietary assessment methods [23–26]. Based on this evidence, a modest correlation coefficient of *r* = 0.5 is considered a good indicator of validity for determining the sample size needed to evaluate the agreement between our clinical FFQ and 24-hour recall [27]. Using G*Power software [28], a priori sample size calculation was conducted for a two-tailed correlation analysis with statistical power = 0.8, alpha = 0.05, and r = 0.5. The analysis indicated that a minimum of 29 participants would be needed to detect a significant correlation between the FFQ and recall measures.

In addition, recent evidence suggests that a sample of approximately 13 participants is sufficient to reach saturation in qualitative studies with a small number of clear objectives (*See Section 3*.*4*.*2*: *Feasibility assessment of FFQ*) [29]. Therefore, the planned sample of 29 participants will be sufficiently powered to evaluate the qualitative evidence and feedback. Nonetheless, to account for an anticipated dropout rate of 20% as well as to accommodate any potential missing/incomplete data, the target sample size will be increased to 50 participants (**Fig 2**) [30, 31]. Furthermore, 25 healthcare professionals consisting of nurses, dietitians, and clinicians at RSUTH will be purposely recruited to provide qualitative feedback on the food frequency questionnaire.

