### Statistical analysis

Statistical analyses will be conducted using R programming language version 4.3.0 [35] with significance level set at p<0.05. Descriptive statistics will be used to analyse categorical and continuous variables. Categorical demographic variables will be analysed using frequency distribution, while continuous demographic variables will be summarised as mean and standard deviation for normally distributed variables and median and interquartile range (IQR) for non-normally distributed variables. As the frequencies of food groups are not normally distributed, differences in frequencies between the two FFQs (FFQ1 vs. FFQ2) and between the two methods (24 HR vs. FFQ2) in phase 1 will be tested using Wilcoxon’s signed-rank test.

Feasibility and acceptability will be assessed through descriptive analyses, including means and 95% confidence intervals (CI), qualitative feedback, and content analysis of indicators related to the process (e.g., proportion interested, started, completed FFQ) and resource (e.g., time to complete and review, rated performance, and practicality).

The West African Food Composition Table will be used to calculate the nutrient content (macronutrients such as energy, carbohydrates or sugar, proteins, fats, and fibre and minerals such as sodium and potassium) of the foods reported in both the FFQ and 24HR. The mean and distribution of nutrient intakes obtained from the FFQ and 24HR will be calculated, and a comparison will be made to assess the differences using the Wilcoxon signed-rank test. Pearson correlations will be used to calculate the correlation coefficients between the FFQ and 24HR for each nutrient to assess the agreement between the FFQs and 24HR and the reproducibility of the FFQs. Additionally, the agreement between the FFQ and the average of three 24-hour dietary recalls will be estimated using Intraclass Correlation Coefficient (ICC), de-attenuation of the correlation coefficients, or quintile cross-classification analysis and the Bland-Altman plots will be used to visualise the agreement between the recalls and FFQ [36–38].

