Feedback from clinical patients and healthcare professionals regarding the FFQ’s feasibility is expected to drive its refinement within a user-friendly clinical context. This could potentially bridge the gap between nutritional guidelines and clinical care, equipping healthcare professionals to systematically assess the dietary intake of patients for diagnostic and preventive purposes and enable clinicians to provide region-specific dietary recommendations, fostering improved disease prevention and management, including hypertension [49]. The anticipated findings from the Intraclass Correlation Coefficient (ICC) analysis and correlations between the FFQ and 24-hour dietary recall (24HR) are poised to illuminate the FFQ’s reproducibility and validity in assessing dietary intake. Strong ICC values and correlations above 0.4 would indicate the FFQ’s reliability and accuracy in capturing habitual dietary patterns, which is crucial for providing accurate dietary advice to patients [44, 50, 51]. The scoring system for the FFQ could offer a practical means of categorising habitual dietary habits. Should the scoring system align with established dietary recommendations and scientific evidence, it could be a valuable tool for clinicians to assess dietary quality and offer tailored dietary guidance to patients. The assessment of the acceptability of the FFQ. Positive feedback could indicate that the FFQ is well-received by clinical patients and that its implementation could be feasible in a clinical setting. This information is essential for potentially integrating the FFQ into routine clinical practice.

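### Pearson r is the only coefficient named for FFQ reproducibility and the lead one for agreement with recalls, although it ignores systematic shift and fits poorly with the plan's own non-normality statement; an "or" leaves the supporting validity statistics open

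*Protocol article*

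**What the plan says.** In the protocol article, Statistical analysis, the per-nutrient coefficient is fixed: "Pearson correlations will be used to calculate the correlation coefficients between the FFQ and 24HR for each nutrient". The same sentence gives it two uses, agreement between FFQ and recalls and reproducibility of the FFQ. No transformation or rank version is mentioned.

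Earlier in that section, Wilcoxon signed-rank tests are chosen for FFQ1 versus FFQ2 and for recalls versus FFQ2, with the reason "As the frequencies of food groups are not normally distributed". Wilcoxon is chosen again for nutrient intakes, but there only for FFQ versus recalls.

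For the FFQ against the mean of the three recalls, agreement is also to be "estimated using Intraclass Correlation Coefficient (ICC), de-attenuation of the correlation coefficients, or quintile cross-classification analysis", with Bland-Altman plots in addition. No ICC is named there for FFQ1 versus FFQ2.

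Two other places bear on this. Validation and reproducibility of the FFQ defines reproducibility as the level of agreement between the two administrations. The Discussion says "The anticipated findings from the Intraclass Correlation Coefficient (ICC) analysis and correlations between the FFQ and 24-hour dietary recall (24HR) are poised to illuminate" both reproducibility and validity, and reads correlations above 0.4 as a sign of reliability and accuracy. It does not say whether that means raw or de-attenuated values.

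**The concern.** Three things do not fit together.

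- **Coefficient and data.** The section treats the data as unsuited to normal-theory tests of difference, then relies on Pearson r for nutrients computed from those foods. If the intakes are skewed, a few large values can dominate r at this sample size.
- **Coefficient and target.** Reproducibility is defined as agreement, but Pearson r measures linear association. If patients report systematically more or less at the second administration, r does not change. For nutrients, no other planned FFQ1-FFQ2 analysis would show the shift.
- **Open choice.** ICC, de-attenuation and cross-classification answer different questions. Joined by "or", they allow the choice to be made after the data are seen, and the 0.4 benchmark can be met or missed according to whether r is corrected.

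Validation of the tool is central to the primary outcome, and correlation coefficients are the named measure for the secondary agreement outcome, so the choice affects a main conclusion of the study.

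**Working it through.** **1. The plan's own figure.** The sample size rests on a "two-tailed correlation analysis with statistical power = 0.8, alpha = 0.05, and r = 0.5", giving "a minimum of 29 participants would be needed to detect a significant correlation between the FFQ and recall measures". By Fisher's z, n = ((1.960 + 0.842)/atanh(0.5))² + 3 = (2.802/0.549)² + 3 = 29.01. A bivariate-normal simulation of the t-test for r (100,000 runs) gives power 0.799 at n = 28 and 0.815 at n = 29. The figure of 29 reproduces. With "an anticipated dropout rate of 20"%, 29/0.8 = 36.25, so 37 would do; the target of 50 leaves about 50 × 0.8 = 40 completers. The sample size is not at fault.

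**2. Reproducibility: what Pearson r misses.** For equal SDs and a shift of d SDs between FFQ1 and FFQ2, absolute agreement is 2r/(2 + d²). The value r = 0.7 is illustrative.

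- d = 0: 1.4/2 = 0.70
- d = 0.5: 1.4/2.25 = 0.62
- d = 1: 1.4/3 = 0.47

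Pearson r is 0.70 in all three cases. This step needs no assumption about skew.

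**3. The open choice and the 0.4 benchmark.** With three recalls averaged, de-attenuation multiplies r by √(1 + λ/3), where λ is the within/between-person variance ratio of a single recall. The article gives no λ, so I assume 1 to 6.

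| λ | Factor | Observed 0.30 becomes | Observed r needed to reach 0.4 |
|---|---|---|---|
| 1 | 1.15 | 0.35 | 0.35 |
| 3 | 1.41 | 0.42 | 0.28 |
| 6 | 1.73 | 0.52 | 0.23 |

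At λ = 3, any observed r from 0.28 to just under 0.40 misses the benchmark raw and meets it corrected.

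**4. Pearson under skew.** The article gives no spread for nutrient intake. I assume lognormal intakes with log-scale r = 0.5 and n = 50 (20,000 simulated samples per row). The SD of r is 0.11 on logged values and 0.115 for Spearman, whatever the skew. Their chances of reaching 0.4 are about 0.82 and 0.75.

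| Log-SD (assumed) | Mean raw r | SD of raw r | Chance raw r ≥ 0.4 |
|---|---|---|---|
| 0.3 | 0.49 | 0.117 | 0.78 |
| 0.5 | 0.47 | 0.129 | 0.71 |
| 0.8 | 0.43 | 0.157 | 0.57 |
| 1.0 | 0.41 | 0.178 | 0.49 |
| 1.2 | 0.38 | 0.196 | 0.43 |

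Part of the fall in the last column is a lower population value, not only noise: on the raw scale it is (e^{0.5s²} − 1)/(e^{s²} − 1), which is 0.489 at s = 0.3 and 0.378 at s = 1.0. With 40 completers the SDs are 0.131 (raw) versus 0.123 (log) at log-SD 0.3, and 0.192 versus 0.122 at 1.0.

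**The case against.** Several stronger readings are tempting, and the article does not support them.

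- **That the ICC is applied to the wrong pair.** FFQ and recalls are both converted to nutrients with one food composition table, so they share units. An ICC between them is legitimate, and it should fall when one method is biased. The gap is that no ICC is named for FFQ1 versus FFQ2.
- **That the Discussion reserves the ICC for reproducibility.** It ties the ICC and the correlations jointly to reproducibility and validity.
- **That the correlations will be unstable.** Non-normality is stated for food-group frequencies. Skewed nutrients are an inference, though the choice of Wilcoxon for nutrients fits it. At log-SD 0.3 the loss is small.
- **That failing to adjust for energy is an error.** The article is silent on it, and such detail may sit in a fuller plan.
- **That validity rests on Pearson alone.** Bland-Altman plots, Wilcoxon comparisons and at least one supporting statistic are also planned, and the 0.4 value is Discussion text rather than a formal pass rule.

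It is also fair to say that the FFQ1-FFQ2 Wilcoxon test looks for a systematic shift. It does so for food-group frequencies only, and a test of difference does not quantify agreement. Finally, leaving r uncorrected understates validity, so omitting de-attenuation is conservative. That stands, but it does not settle which value is compared with 0.4.

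**Conclusion.** The point holds in a limited form and should be corrected. Two parts need no assumption about the data's distribution. The only coefficient named for reproducibility cannot register a systematic shift, although reproducibility is defined as agreement: in the example, r stays at 0.70 while absolute agreement falls to 0.62 or 0.47. The supporting validity statistics are also left as alternatives, with the 0.4 benchmark not attached to raw or corrected r; how far that matters depends on the variance ratio, and at an assumed ratio of 3 an observed 0.30 becomes 0.42.

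The third part is conditional. Untransformed Pearson r sits poorly beside the section's own non-normality statement, but its cost ranges from slight (SD of r 0.117 at log-SD 0.3) to substantial (0.178 at log-SD 1.0), against about 0.11 for logged values or Spearman. The documents do not show where these nutrients fall in that range.

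**What to change.** In Statistical analysis:

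- For FFQ2 versus the mean of the three recalls, use Spearman, or Pearson on log-transformed intakes. Report it both raw and de-attenuated, with 95% CI.
- State which of the two the 0.4 benchmark in the Discussion refers to.
- For FFQ1 versus FFQ2, add an ICC and specify the absolute-agreement form, since a consistency form would also ignore a shift.
- Keep the ICC and Bland-Altman plots for FFQ versus recalls.
- Replace "or" by "and" in the list of ICC, de-attenuation and cross-classification, so that all three are reported.
- Energy-adjusted correlations may be added as a supplementary analysis; energy intake is already computed.

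The cost is a few sentences and a few lines of code. No new data, visits or patients are needed.

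### Pearson correlation, with no transformation or rank correlation beside it, is named for nutrient agreement and reproducibility, although the same section uses a rank test on these nutrient intakes

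*Protocol article*

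**What the plan says.** All of this is in the protocol article.

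- **Statistical analysis, distribution.** The choice of the Wilcoxon signed-rank test for FFQ1 versus FFQ2 and for recall versus FFQ2 is justified with "As the frequencies of food groups are not normally distributed". The same test is then chosen for differences in nutrient intake between FFQ and recall.
- **Statistical analysis, correlation.** The next sentence reads "Pearson correlations will be used to calculate the correlation coefficients between the FFQ and 24HR for each nutrient", and goes on to cover both agreement with the recalls and reproducibility of the FFQ. It mentions no transformation, normality check or rank correlation.
- **Statistical analysis, other measures.** The section adds the ICC, de-attenuation or quintile cross-classification, and Bland-Altman plots to visualise agreement.
- **Sample size and sampling technique.** The study is sized by a "two-tailed correlation analysis with statistical power = 0.8, alpha = 0.05, and r = 0.5", giving "a minimum of 29 participants would be needed to detect a significant correlation between the FFQ and recall measures". After allowance for 20% dropout and incomplete data, "the target sample size will be increased to 50 participants".
- **Discussion.** Strong ICC values and correlations above 0.4 are to be read as showing that the FFQ is reliable and accurate.

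**The concern.** Within one section, nutrient intakes are handled as needing a rank test for differences but as suitable for a moment-based correlation. The nutrients are computed from the foods reported, and for the FFQ those are the frequencies that the section calls non-normal.

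Pearson's coefficient on right-skewed positive data has two weaknesses. It is usually smaller than the correlation on a scale where the data are closer to normal, and a few heavy consumers can dominate it. The usual confidence interval, based on Fisher's z, is then too narrow as well.

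This matters because the Outcomes section makes correlation coefficients the measure of agreement between the two methods, and the Discussion sets a benchmark for them. Whether a nutrient falls above or below 0.4 should not turn on one patient's intake. It should also not depend on a choice of scale made after the data are seen.

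**Working it through.** **Inputs from the protocol.** Two-sided alpha 0.05, power 0.8, r = 0.5, minimum 29, target 50, dropout 20% (Sample size and sampling technique); benchmark 0.4 (Discussion).

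**Assumptions, not in the documents.** Both instruments give lognormal intakes with the same CV, and the correlation is 0.5 on the log scale. CV is varied over 0.3, 0.5, 0.8 and 1.0.

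**Step 1: the plan's own figure.** With Fisher's z,

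N = ((1.960 + 0.842) / atanh(0.5))² + 3 = (2.802 / 0.5493)² + 3 = 29.01, or 28.2 with the bias correction.

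Simulating the t-test of r under bivariate normality gives power 0.797 at 28 and 0.815 at 29. The stated 29 is therefore correct for bivariate normal data. Dropout: 29 / 0.8 = 36.25, so 37; the target of 50 leaves 50 × 0.8 = 40 completers.

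**Step 2: what skew does to the coefficient.** For lognormal margins with log-scale SD s and log-scale correlation 0.5, the correlation on the untransformed scale is

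r = (exp(0.5 s²) − 1) / (exp(s²) − 1), with exp(s²) = 1 + CV², so r = (√(1 + CV²) − 1) / CV².

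- CV 0.3: (1.0440 − 1) / 0.09 = 0.489
- CV 0.5: (1.1180 − 1) / 0.25 = 0.472
- CV 0.8: (1.2806 − 1) / 0.64 = 0.438
- CV 1.0: (1.4142 − 1) / 1.00 = 0.414

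**Step 3: sampling behaviour at n = 50 (simulation).**

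| | Log scale | CV 0.3 | CV 0.5 | CV 0.8 | CV 1.0 |
|---|---|---|---|---|---|
| Population r | 0.50 | 0.49 | 0.47 | 0.44 | 0.41 |
| Share of data sets with r > 0.4 | 82% | 78% | 72% | 62% | 56% |
| Coverage of nominal 95% Fisher interval | 95% | 93% | 91% | 86% | 84% |
| Deleting one patient moves r by ≥ 0.1 | 3% | 13% | 25% | 43% | 51% |

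Coverage is for the untransformed population r in that column. The protocol does not say that it will attach intervals to the correlations, so this row applies only if the customary interval is reported.

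**Step 4: power of the untransformed Pearson test.**

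| n | Log scale | CV 0.3 | CV 0.5 | CV 0.8 | CV 1.0 |
|---|---|---|---|---|---|
| 29 (minimum) | 81% | 78% | 74% | 66% | 62% |
| 40 (after 20% dropout) | 92% | 90% | 87% | 79% | 74% |
| 50 (target) | 97% | 95% | 93% | 87% | 82% |

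If the planning value of 0.5 is taken to hold on the untransformed scale, power at n = 29 is 79%, so almost nothing is lost. Spearman under the same log-scale model has power of 76%, 88% and 95% at n = 29, 40 and 50.

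**The case against.** The strongest reply has five parts.

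1. **Power.** A reader might infer that the study loses the power it was sized for. The documents do not support that. The sample size section takes 0.5 from earlier FFQ-recall studies without giving a scale, and 29 is a minimum while 50 are enrolled. At 50, power stays above 80% over the whole CV range. With 40 completers it falls below 80% only from a CV of about 0.8. This part of the reply stands.
2. **Scale and distribution.** The protocol never says that intakes are analysed untransformed, and its explicit non-normality statement concerns food-group frequencies. For nutrients, non-normality is only implied by the choice of Wilcoxon. This also stands. Even so, an analyst following the text would compute Pearson on intakes as calculated.
3. **Skewness.** It is assumed. Energy or protein summed over many foods, with recalls averaged over three days, may be only mildly skewed. The five FFQ response categories also cap each item's frequency, so lognormal tails may exaggerate the influence of one patient. This is fair, and it is why the range starts at CV 0.3.
4. **Direction.** A reader might infer that r is always lowered. It is not: a patient extreme on both instruments can raise it.
5. **Role of the coefficient.** The 0.4 is a Discussion benchmark, not a decision rule, and other agreement measures are listed. That is true, but the rank-based one, quintile cross-classification, is offered only as an alternative. The effect of skew on the ICC and the Bland-Altman plots was not simulated here.

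The reply that a transformation is ordinarily left to an analysis plan does not dispose of the point. The article itself fixes the method, and that method sits badly with the distributional premise in the same section.

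**Conclusion.** The point holds in a limited form. The section uses a rank test for nutrient differences and then names Pearson, without transformation or rank alternative, for agreement and reproducibility of the same nutrients.

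Under the stated assumptions the consequence at n = 50 runs from slight at CV 0.3 to material at CV 0.8 to 1.0. At the upper end, a tool with a log-scale correlation of 0.5 passes 0.4 in only 56% to 62% of data sets, and one patient can move r by at least 0.1 in 43% to 51%. The real CV of each nutrient is unknown, so these figures are a range and not a prediction.

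The sample size calculation is not in error, and no general shortfall in power follows.

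**What to change.** In the Statistical analysis section, state that nutrient intakes from FFQ and recall will be log-transformed, with a small constant added where zeros occur, before the Pearson correlation, the ICC and the Bland-Altman analysis. State also that Spearman's coefficient will be reported alongside for each nutrient. Spearman alone would not give 80% power at the minimum of 29 under the model above, but it does at 40 and 50.

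The cost is a sentence or two of wording and no new data. The small downside is that Bland-Altman differences are then read as ratios instead of grams or milligrams. Fixing the scale before analysis also removes any choice of scale once it is known on which side of 0.4 a nutrient falls.

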#### Validation and reproducibility of the FFQ

The FFQ will be administered to clinical patients (*n* = 50) twice (i.e., first and third visits) to quantify the intake of food items. Additionally, an inconsecutive three (3) repeated 24HR, including two weekdays and one weekend day, will be used to collect dietary information from the clinical patients for the past 24 hours using the multiple-pass method [21, 22] at the time of visits and intervals between the two FFQs administrations (**Fig 1**). The reproducibility of the FFQ will be assessed by measuring the level of agreement between the two administrations of the FFQ. Furthermore, the validation will be assessed by evaluating the agreement level between the FFQ and the average of the three 24-hour recalls [32, 33]. Healthcare professionals are not involved in the patient FFQ validation stage.

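### FFQ reproducibility is defined as agreement between two administrations, but the only coefficient named for it is Pearson correlation; the ICC and Bland-Altman plots are written only for FFQ versus recall

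*Protocol article*

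**What the plan says.** Three sections of the protocol article bear on this, and Outcomes lists reproducibility among the results to be described under the primary outcome.

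- **Validation and reproducibility of the FFQ** sets the aim: "The reproducibility of the FFQ will be assessed by measuring the level of agreement between the two administrations of the FFQ". Fifty patients complete the FFQ at the first and third visits.
- **Statistical analysis** gives the methods. For food groups, "differences in frequencies between the two FFQs (FFQ1 vs. FFQ2) and between the two methods (24 HR vs. FFQ2) in phase 1 will be tested" by Wilcoxon's signed-rank test. For nutrients, "Pearson correlations will be used to calculate the correlation coefficients between the FFQ and 24HR for each nutrient", and the purpose given is "to assess the agreement between the FFQs and 24HR and the reproducibility of the FFQs". The next sentence says that "the agreement between the FFQ and the average of three 24-hour dietary recalls will be estimated using Intraclass Correlation Coefficient (ICC", with de-attenuation or quintile cross-classification, and that "Bland-Altman plots will be used to visualise the agreement between the recalls and FFQ".
- **Discussion** starts from "The anticipated findings from the Intraclass Correlation Coefficient (ICC) analysis" and the FFQ-recall correlations and says that these "are poised to illuminate the FFQ’s reproducibility and validity in assessing dietary intake". It takes strong ICC values, with no number attached, and correlations above 0.4 as signs of reliability and accuracy.

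**The concern.** The stated aim is agreement, but the coefficient named for it measures linear association. Taken literally, the Pearson sentence correlates the FFQ with the recall, and that pair carries no direct information on whether the FFQ repeats itself. Taken generously as FFQ1 against FFQ2, it still uses a statistic that ignores any shift or rescaling between administrations. The measures that do respond to such changes, the ICC and Bland-Altman plots, are written only for FFQ versus recall. The Discussion then relies on the ICC for reproducibility, although no FFQ1-FFQ2 ICC is specified.

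At stake is the reproducibility claim within the primary outcome. For nutrients it could rest on a coefficient that stays high while patients report systematically different intakes three weeks into the study.

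**Working it through.** **1. The plan's own figure.** The sample size section gives 29 participants for r = 0.5, two-sided alpha 0.05 and power 0.8. By Fisher's z, n = ((1.960 + 0.842) / atanh 0.5)² + 3 = (2.802 / 0.5493)² + 3 = 29.01, so the figure reproduces. It concerns the FFQ-recall correlation; the section gives no planning value for FFQ1 against FFQ2. The test-retest inputs below are therefore assumptions.

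**2. Which statistic serves which pair, as written.**

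| Pair | Association | Agreement | Location |
|---|---|---|---|
| FFQ1 vs FFQ2, food groups | none named | none named | Wilcoxon |
| FFQ1 vs FFQ2, nutrients | Pearson (by stated purpose only) | none named | none named |
| FFQ vs recall, nutrients | Pearson | ICC, Bland-Altman | Wilcoxon |

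**3. Pearson against agreement under a proportional drop.** For two measurements with SDs s1 and s2, correlation r and mean difference d, the population two-way absolute-agreement single-measure ICC is

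ICC = 2·r·s1·s2 / (s1² + s2² + d²).

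Assume an FFQ1 mean of 1, coefficient of variation 0.6 and r = 0.70. If FFQ2 is c times FFQ1 in level and spread, then s1 = 0.6, s2 = 0.6c and d = 1 − c.

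- c = 0.8: 0.4032 / (0.36 + 0.2304 + 0.04) = 0.64
- c = 0.7: 0.3528 / (0.36 + 0.1764 + 0.09) = 0.56
- c = 0.6: 0.3024 / (0.36 + 0.1296 + 0.16) = 0.47

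Pearson is 0.70 in all three cases.

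**4. Other assumptions.** With equal SDs and a shift of 0.25, 0.5 or 1 SD, the ICC is 0.78, 0.71 or 0.53 if r = 0.8, and 0.48, 0.44 or 0.33 if r = 0.5. Pearson stays at 0.8 or 0.5. A small shift costs little and a large one costs a lot.

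**5. What the planned Wilcoxon test would catch.** Simulated with normal data in the step 3 scenario, its power for drops of 20%, 30% and 40% is about 0.8, 0.99 and 1.00 at n = 40 (50 less the 20% dropout), and about 0.9, above 0.99 and 1.00 at n = 50. For a pure shift at r = 0.7 and n = 40, power is 0.50 for 0.25 SD and 0.97 for 0.5 SD.

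**6. FFQ versus recall.** Since 2·s1·s2 cannot exceed s1² + s2², the ICC cannot exceed r when r is positive. Over the article's quoted range of r = 0.3, 0.5 and 0.7, it is therefore at most 0.30, 0.50 and 0.70. With an assumed 0.5 SD shift and an SD ratio of 0.7, it is 0.24, 0.40 and 0.56.

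**The case against.** The strongest reply is that a systematic change is already tested. A reader might infer from the Pearson sentence that a general fall in reported intake would pass unnoticed, and the article does not support that. The Wilcoxon comparison of FFQ1 with FFQ2 is planned. Nutrients are derived from reported foods through a composition table, so a fall in all intakes would largely appear in the food-group frequencies, where step 5 shows good power for moderate shifts. This stands and narrows the point. It does not close it: the test is not stated for FFQ1-FFQ2 nutrients, single food groups may be noisier than the simulation, and a non-significant location test does not show agreement, because individual differences that cancel out leave it unmoved.

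A second reply is that the Discussion suggests an FFQ1-FFQ2 ICC was intended, and that an article may leave the form of the ICC to a fuller document. Both are fair. The defect may be incomplete wording rather than a deliberate choice, and the unstated ICC form is no fault here. But the article does assign each statistic to a pair, and those assignments do not deliver the aim it sets.

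Two further inferences should be resisted. One is that the ICC is misplaced on FFQ versus recall. Agreement is the stated objective for that pair, both instruments use the same composition table, and the ICC stands beside correlation and Bland-Altman plots, with de-attenuation named as an option. The other is that a strong FFQ-recall ICC cannot be reached. Strong has no number, and the quoted range lets r, and so the ICC, reach 0.7.

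**Conclusion.** The point holds in a limited form. The three sections do not agree on how reproducibility is measured, and the one coefficient named for it cannot measure agreement, whichever pair it is computed on. That Pearson is blind to shift and scale needs no assumption. The size does: at an assumed r of 0.70 and coefficient of variation of 0.6, a 20% to 40% drop opens a gap of 0.06 to 0.23 between Pearson and the absolute-agreement ICC (0.70 against 0.64 to 0.47). If the two administrations have the same mean and spread, the two coefficients coincide.

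The consequence is a nutrient reproducibility figure that may be too favourable, with no planned measure of how far the two administrations differ. It is not that any shift would be missed. For FFQ versus recall, the supportable remark is only that the ICC is capped by r, so about 0.5 is the most to expect at the planning value.

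**What to change.** In Statistical analysis, state that FFQ1 and FFQ2 are compared per nutrient by a two-way absolute-agreement, single-measure ICC with 95% confidence interval, and by Bland-Altman limits of agreement. Keep correlation and the Wilcoxon test as supplements. Reword the Pearson sentence so that FFQ-recall correlations serve validity only. The FFQ-recall ICC may stay as one of several validity measures, interpreted separately from reproducibility and with its ceiling at r in mind. Then make Validation and reproducibility of the FFQ, Statistical analysis and Discussion name the same statistic for the same pair.

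The cost is wording and a small amount of analysis. Both FFQ administrations are already scheduled, so no data collection changes. The downside is that reproducibility may look slightly less favourable than under Pearson correlation.
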